### Secondary outcome

The secondary outcomes are the need for pain relief during menstruation and potential side effects of EMDR therapy.

### Study procedure

After obtaining permission from the human ethics committee at Qazvin University of Medical Sciences, registering it at the Iranian Clinical Trial Registration Center, and obtaining required permissions from university authorities, the researcher will visit the female dormitories at Qazvin University of Medical Sciences to invite potential participants for this study. There are four dormitories for female students at Qazvin University of Medical Sciences. The researchers will provide the information on the purpose of the research, type of intervention, and confidentiality arrangement for the research data. The participants will be asked to sign the written consent form before enrolling in the study. The researchers also ensure the participants that they can leave the study at any time and can benefit from commonly used palliative treatments whenever they are not willing to continue to participate or when they have severe pain and discomfort related to dysmenorrhea.

During recruitment, potential participants will be initially assessed for the pain intensity related to primary dysmenorrhea monthly for 2 months. Eligible individuals will be randomly assigned to EMDR therapy and control (no intervention) groups by a simple random blocking method with four blocks. EMDR therapy will be performed in the intervention group. The follow-up evaluation of dysmenorrhea pain will be performed in both groups at 1 and 2 months after the last treatment session. The flowchart of the research procedure is presented in Fig. 1.

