### Intervention

EMDR therapy will be performed in the intervention group. The participants are expected to attend all scheduled interventions in which the EMDR therapy will be implemented to manage their distressing memories of severe pain due to dysmenorrhea. The expected outcome is that the level of subjective distress will be reduced and positive cognition will be reorganized [27]. The EMDR therapy consists of eight essential phases, and several steps may be performed during one session:

Phase 1

This includes taking the history of the unpleasant condition, designing the treatment protocol, and preparing and evaluating the participant. This helps the therapist to determine the specific target to achieve. To identify this target, participants will be asked to talk about their memories of the menstruation, dysmenorrhea, and menstruation-related complaints as well as the epicenter of the pain. Then they will be asked to specify the traumatic event which disturbed them the most.

Phase 2: Preparation

Prior to initiation of the intervention for the first time, therapeutic targets should be established. The procedure of EMDR therapy and its effects and safety should be explained to the participants. Their questions and concerns should be addressed.

Phase 3: Assessment

In this phase, the components of the therapeutic target should be identified. When the memory has been identified, the participant will be asked to select the image that best stands for that memory. Then the participant will be asked to choose a negative cognition that expresses the dysfunctional self-assessment related to the unpleasant condition. In this phase, negative cognition about dysmenorrhea will be identified and the participant will be asked to imagine the worst picture about their dysmenorrhea. Then they will be asked to choose a positive cognition to be used to replace the negative cognition during the installation phase. They are encouraged to imagine having a less painful menstruation as a positive cognition.

Phase 4: Desensitization

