### Number of intervention sessions

The number of intervention sessions was determined based on previous studies that used EMDR therapy for chronic pain management. A systematic review on the effect of EMDR therapy on chronic pain showed that 1–12 sessions (average of 6 sessions) were used to treat chronic pain. Longer sessions were used in cases of longer-term chronic pain [31]. As a result, the number of treatment sessions for this study has been set at 6, which will be held twice a week. The duration of each session is 30–90 min; this is based on the participants’ willingness and convenience [41]. Given that some participants may respond to the intervention and achieve the target before completing all of the sessions, the intervention will be continued for one more session. Then it will be documented in the final report. No intervention will be performed for the control group, but they will be asked to report their routine strategies to relieve menstrual pain.

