### Sample size calculation

According to previous studies [47, 48], for an effect size of 0.25, power of 0.80, and alpha of 0.05, the sample size is to be 82 subjects (*n* = 41 in each group) using G-Power software. Given the probability of a 10% dropout rate, 44 subjects will be included in each group. The total sample size will be 88 participants.

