### Statistical analysis

Data will be analyzed by using SPSS version 25 software. First, the normal distribution is confirmed by using the Kolmogorov–Smirnov test. If the data are normally distributed, analysis of variance (ANOVA) with repeated measures will be used to compare the mean scores of pain between the groups at different time points. If this is significant, appropriate post hoc tests will be used. A *P* value of less than 0.05 will be considered significant.

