### Ethical and safety issues

The research protocol has been reviewed and approved by the human ethics and research committee of Qazvin University of Medical Sciences (reference number: IR.QUMS.REC.1397.100). It has also been registered in the Iranian Registry of Clinical Trials (IRCT20180823040851N1 in 2018-10-06).

In addition, the following ethical considerations will be respected during the research: obtaining informed consent from the students, the voluntary nature of the participation in this research, and the ability to withdraw from the study at any time. At the beginning and end of the study, the participants will be assured that all of the collected data are completely confidential, and their identity will remain anonymous in any presentations and publications arising from this study. In addition, before the commencement of the first treatment session, the participants will be provided with a brief explanation of EDMR therapy. The research goals will be shared with them and they will be informed of the significance of their cooperation, which will help those suffering from similar thoughts and negative emotions due to dysmenorrhea. The criteria for performing the clinical trial will be considered in the research. Furthermore, EMDR therapy will be freely available to the participants in the control group on request after the completion of this study.

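### Repeated-measures ANOVA, on its natural reading, keeps only women with every VAS rating, and the exit wording does not keep women who stop EMDR in follow-up, so the pain comparison can be biased in either direction

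*Protocol article*

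**What the plan says.** **Leaving.** The Study procedure section tells women that they are free to leave whenever they choose and that they "can benefit from commonly used palliative treatments whenever they are not willing to continue to participate". The same sentence goes on to allow palliative treatment "or when they have severe pain and discomfort related to dysmenorrhea", which does not require leaving. Ethical and safety issues repeats "the ability to withdraw from the study at any time". The next paragraph of Study procedure plans follow-up ratings in both groups at 1 and 2 months after the last session.

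**Sessions.** The Intervention section says: "The participants are expected to attend all scheduled interventions". Number of intervention sessions sets six sessions of 30–90 minutes, twice a week, for the EMDR arm and no intervention for controls. It also provides for early responders, as "some participants may respond to the intervention and achieve the target before completing all of the sessions, the intervention will be continued for one more" (one further session, which is documented).

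**Analysis.** If the data are normal, "analysis of variance (ANOVA) with repeated measures will be used to compare the mean scores of pain between the groups at different time points", in SPSS 25. The SPSS procedure is not named. The Abstract gives four VAS ratings: two before the intervention, used for eligibility, and two after it.

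**Dropout.** After arriving at 82 women, the Sample size calculation says: "Given the probability of a 10% dropout rate, 44 subjects will be included in each group".

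**The concern.** Two statements in the article work together. For a woman who no longer wants to continue, the text describes leaving the study. It does not describe stopping the sessions while still giving the two follow-up ratings. Repeated-measures ANOVA in its classical form then needs a complete set of ratings for each woman, so one missing follow-up VAS removes her, including the ratings she did give.

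The demands fall on one arm. EMDR women attend six sessions and work on their worst memory of menstrual pain, while controls have nothing to stop. The Blinding section says neither participants nor researchers can be blinded, so a woman's view of whether EMDR is helping may affect whether she stays. If loss differs between arms and is related to pain, the analysis compares women who stayed and no longer compares the groups as randomised. Even where loss is unrelated to pain, usable ratings are discarded in a trial with little spare sample.

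**Working it through.** **1. Does the plan's own sample size fit a complete-case repeated-measures ANOVA?**

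Inputs from Sample size calculation: effect size 0.25, power 0.80, alpha 0.05. Input from the Abstract: m = 4 ratings. Assumed: the effect size is Cohen's f, and the correlation between ratings is 0.5.

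For the between-groups test, λ = N·f²·m / (1 + (m − 1)ρ), referred to a noncentral F on 1 and N − 2 degrees of freedom.

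λ = 82 × 0.0625 × 4 / (1 + 3 × 0.5) = 20.5 / 2.5 = 8.2, giving power 0.808. N = 82 is the smallest even total that reaches 0.80. Other set-ups do not reproduce it: m = 3 gives 86, m = 2 gives 98, the within-between interaction with m = 4 gives 24, and one-way ANOVA gives 128.

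So 82 is reproduced as a four-rating repeated-measures ANOVA. Adding women for dropout on top of it fits the reading that dropouts are not analysed.

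**2. How many women would remain?**

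The two pre-intervention ratings are needed for eligibility, so after randomisation only the two follow-up ratings can be lost.

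| Loss | Calculation | Women left | Power (formula above) |
|---|---|---|---|
| Single 10% dropout | 88 × 0.9 = 79.2 | about 79 | 0.79 |
| Each follow-up missed independently by 10% (assumption) | 88 × 0.9 × 0.9 = 71.3 | about 71 | 0.75 |

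Both fall below 82. In the second case 1 − 0.1² = 99% of women would still have at least one follow-up rating, so most of those deleted would have had usable data.

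**3. How large could the bias be?**

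The article gives no VAS standard deviation, no correlation, no dropout by arm and no outcomes for leavers. Assumptions: no true effect; 44 per arm; four ratings each with SD 1 and pairwise correlation 0.5; about 10% of an arm lost (4 of 44); complete cases only; arms compared on mean follow-up minus mean pre-intervention VAS; 10,000 simulated trials per scenario.

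| Who leaves | Bias (SD of one rating; negative favours EMDR) | Type I error |
|---|---|---|
| 4 EMDR women at random | 0.00 | 5.0% |
| 4 EMDR women with the worst change | −0.12 | 14.5% |
| 4 EMDR women with the best change | +0.12 | 14.6% |
| 4 with the worst change in each arm | 0.00 | 7.8% |

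On units: the variance of a mean of two ratings is (1 + 0.5)/2 = 0.75. The variance of the change is 0.75 + 0.75 − 2 × 0.5 = 0.5, so its SD is 0.71. A bias of 0.12 SD of one rating is therefore 0.12/0.71 = 0.17 SD of the change score.

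The second and third rows are extremes, because leaving is determined entirely by the outcome. Partial selection would fall between them and zero.

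**The case against.** The strongest reply is that this is a condensed article. Retention after stopping treatment, the analysis set and the handling of missing ratings commonly belong to the full protocol or the SAP, neither of which is shown. That stands: their absence is not a finding. What remains is a method that the article does name, and exit wording that it does state. A later analysis plan could change the model, but it could not recover ratings that were never collected.

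Several stronger readings are tempting and not supported:

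- **Leaving the study is the only way to end treatment.** It is not. Women who reach the target early have one more session, and nothing suggests that they leave. The point is limited to women unwilling to continue.
- **The plan ends data collection when a woman stops EMDR.** The Study procedure sentence is a consent assurance about voluntariness and access to pain relief, not a rule that ends follow-up. Follow-up is planned in both groups without a condition on sessions attended. The fault is that the wording leaves the matter open.
- **SPSS will certainly delete incomplete cases.** Deletion belongs to the classical procedure (GLM Repeated Measures). SPSS MIXED would keep partial data, and the article names neither. ANOVA most naturally means the former.
- **The bias favours EMDR.** Deletion applies to both arms, the 10% is not split by arm, and dissatisfied controls may leave too. Random loss gives no bias, and loss of good responders reverses it.

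It is also fair to say that a mixed model alone does not cure the problem. Women with no follow-up rating still add almost nothing on follow-up pain, and they are the women removed in the simulation.

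**Conclusion.** The point holds as a risk that the named method and the exit wording create together, not as a demonstrated bias. Under the assumptions above, with about 10% loss from the EMDR arm only, the bias runs from zero (random loss) to about 0.12 SD of a single VAS rating in either direction. In the extreme cases the type I error is about 15% against a nominal 5%. Selective loss of poor responders, which would favour EMDR, is plausible because only that arm carries sessions and the trial is unblinded. The article gives no dropout by arm, no reasons and no leaver outcomes that would establish it.

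The loss of information does not depend on direction. Complete-case analysis leaves about 79 women under the plan's own 10% dropout and about 71 under independent 10% loss at each follow-up, against 82 required. The 82 itself rests on reading the effect size as Cohen's f with an assumed correlation of 0.5.

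**What to change.** 1. **Statistical analysis.** Replace repeated-measures ANOVA with a likelihood-based mixed model for repeated measures (SPSS MIXED). Use all available VAS ratings, including the two pre-intervention ones, for every randomised woman in her assigned arm.
2. **Sensitivity analysis.** Add one for women with no follow-up VAS, for example control-based multiple imputation. Filling in a single control-arm mean would understate the variance.
3. **Study procedure.** State that a woman who stops sessions is still asked for both follow-up ratings unless she declines further data collection. Her right to withdraw is unchanged. This is the only step that recovers the missing outcomes, and Trial status says recruitment has not begun.

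The cost is wording in two sections, slightly more analysis work in the same software and a few extra contacts, with no additional participants. The estimated effect may be smaller once women who stopped sessions are included.

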### Sample size calculation

According to previous studies [47, 48], for an effect size of 0.25, power of 0.80, and alpha of 0.05, the sample size is to be 82 subjects (*n* = 41 in each group) using G-Power software. Given the probability of a 10% dropout rate, 44 subjects will be included in each group. The total sample size will be 88 participants.

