**Methods/Design:**

A randomized clinical trial was designed in compliance with the Consolidated Standards of Reporting Trials (CONSORT). Female students who have moderate to severe primary dysmenorrhea (based on a visual analogue scale [VAS] score of at least 4 for two consecutive months) and who live in dormitories at Qazvin University of Medical Sciences in Qazvin, Iran will be invited to participate in the study. The total sample size will be 88 girls, who will be randomly assigned to intervention (*N* = 44) and control (N = 44) groups. EMDR therapy will be performed for the intervention group, while the control group can use sedative or other pain relife methods as their routin... There will be six treatment sessions, which will be held twice a week. The duration of each session is 30–90 min, according to the convenience of each participant. The data will be collected using the demographic characteristics questionnaire, the VAS, the Subjective Units of Anxiety or Distress Scale (SUD), and the Validity of Cognition Scale (VOC). The data on pain intensity due to primary dysmenorrhea in both groups will be collected at 1 and 2 months before the intervention (to identify eligible participants) and 1 and 2 months after the intervention (follow-ups). Data will be analyzed by using SPSS version 25 software and analysis of variance (ANOVA) with repeated measures with appropriate post hoc tests. A *P* value of less than 0.05 will be considered significant.

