### Methods to protect against bias

#### Randomization and allocation

A convenience sampling method will be used for recruitment. The researchers will recruit the female students in dormitories at Qazvin University of Medical Sciences. Eligible participants will be enrolled in the study. They will be randomly assigned to one of two groups by the simple random blocking method with four blocks.

In the block randomization method, the assigning sequence will be written before the commencement of the research. Given that two groups will be studied, four blocks will be used and one letter will be assigned to one group (A: EMDR group; B: control group). All possible modes of the four blocks will be written and numbered as below:1. AABB; 2. ABAB; 3. BBAA; 4. BABA; 5. ABBA; 6. BAAB.

So, in each block, two students will be assigned to the intervention group and two will be assigned to the control group. Then, with a simple random method and the table of random numbers, a number of blocks will be selected from the blocks of numbers. By writing the contents of the blocks for those numbers (as long as the sample size is determined), we will determine the sequence of random allocation. For example, if the numbers are 1, 2, 2, 3, the assigning sequence will be AABB ABAB ABAB BBAA. After the random allocation sequence is generated, it will be numbered from 1 to 88. As a result, every participant will have a unique code.

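### Enrolling 44 per group covers about 6.8% dropout from the required 41 per group, not the stated 10%; the resulting loss of power is small

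*Protocol article*

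**What the plan says.** The Sample size calculation section of the protocol article works in two steps. First, "for an effect size of 0.25, power of 0.80, and alpha of 0.05", "the sample size is to be 82 subjects", that is, 41 in each group, obtained with G-Power. Second, "Given the probability of a 10% dropout rate, 44 subjects will be included in each group", and then "The total sample size will be 88 participants".

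The Abstract repeats the total ("The total sample size will be 88 girls"). The Randomization and allocation section numbers its sequence from 1 to 88, and the Allocation concealment section prepares 88 envelopes. Allocation is 1:1 in blocks of four: in each block, "two students will be assigned to the intervention group and two will be assigned to the control group". The article gives no second dropout rate and no rule for replacing participants who leave.

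**The concern.** The second step presents 44 as what follows from 41 per group and 10% dropout. Neither usual way of allowing for dropout gives 44, and taking 10% off 44 leaves fewer than 41. If the section's own dropout rate occurs, the number left for analysis is below the number the section says is needed for power 0.80.

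At stake is the accuracy of the sample size justification, together with a small amount of power. The Discussion section lists the sample size as a strength, and the Trial status section says recruitment has not begun, so the statement can still be corrected before the first participant enters.

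**Working it through.** **Inputs, all from the Sample size calculation section:** 41 per group (82 in total) before dropout; dropout 10%; enrolment 44 per group (88 in total).

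**1. Inflate for dropout, n/(1 - d).**
- Per group: 41/0.90 = 45.6, rounded up to 46, so 92 in total.
- On the total: 82/0.90 = 91.1, rounded up to 92 for equal groups.

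**2. Try the cruder form, n x (1 + d).**
- Per group: 41 x 1.10 = 45.1.
- On the total: 82 x 1.10 = 90.2.
- Even rounded down, these give 45 and 90. Neither form gives 44 or 88.

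**3. Work back from 44.**
- After 10% loss: 44 x 0.90 = 39.6 per group, against 41.
- In total: 88 x 0.90 = 79.2, about 79, against 82. The shortfall is about 3 evaluable participants, or 92 - 88 = 4 enrolled.
- Dropout that 44 does cover: (44 - 41)/44 = 3/44 = 6.8%.

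Steps 1 to 3 use only the protocol's own figures.

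**4. Effect on power.** This step needs assumptions. The section does not say which test, which type of effect size, how many measurements (m) or what correlation (rho) went into G-Power. I took 0.25 as Cohen's f and used the between-groups F test of a two-group repeated-measures ANOVA:

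lambda = f² x N x m / (1 + (m - 1) x rho), with 1 and N - 2 degrees of freedom and alpha = 0.05.

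*Reproducing the plan's figure.* With m = 4 (two pain ratings before and two after the intervention) and rho = 0.5, lambda at N = 82 is 0.0625 x 82 x 4 / 2.5 = 8.2 and power is 0.808. This is the smallest even N that reaches 0.80, so 82 reproduces. With rho kept at 0.5, other values of m do not give 82: m = 2 gives 98, m = 3 gives 86 and m = 5 gives 78.

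*Power under these settings:*

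| N evaluable | Power |
|---|---|
| 92 | 0.851 |
| 88 | 0.835 |
| 82 | 0.808 |
| 80 | 0.798 |
| 79 | 0.793 |

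*Sensitivity.* The settings m = 4, rho = 0.5 are not the only ones that lead to 82.

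| m | rho | Power at 82 | Power at 79 |
|---|---|---|---|
| 4 | 0.50 | 0.808 | 0.793 |
| 2 | 0.25 | 0.808 | 0.793 |
| 3 | 0.45 | 0.802 | 0.787 |

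Across these settings, power is about 0.80 to 0.81 at 82 and about 0.79 at 79, a loss of about 0.015.

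**The case against.** The strongest reply is that the slip hardly matters. About 3 evaluable participants are missing, and power drops by about 0.015, to roughly 0.01 below target. No estimate, analysis or conclusion would change. That is right, and it limits the weight of the point.

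A second reply is that the section never expressly promises 82 evaluable participants at 10% loss. It says only that, in view of a 10% dropout probability, 44 will be included in each group. That is also true of the wording. But the sentence offers no other reason for going from 41 to 44, and an allowance for 10% dropout has no other natural meaning. Block size does not explain 44 either, since 92 is equally divisible by four (23 blocks).

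A third reply is that the power figures are back-fitted. This stands. They depend on an assumed test, number of measurements and correlation, and must be labelled so. The arithmetic on 41, 10% and 44 does not depend on them.

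A reader might infer from the failed allowance that the trial is seriously underpowered. The documents do not support that: under every setting checked that leads to 82, power at 79 stays close to 0.79.

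**Conclusion.** The point holds as a minor arithmetic error. From 41 per group, a 10% allowance needs 46 per group (92 in total). The planned 44 per group (88 in total) covers 6.8% dropout, and at 10% about 79 remain, about 3 fewer than the 82 required. This part is certain, because it uses only figures printed in one section.

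The consequence is power of about 0.79 instead of 0.80 or slightly above. That figure rests on a between-groups repeated-measures F test with f = 0.25 and on combinations of m and rho chosen because they lead to 82; the protocol states none of these. What needs correcting is the sample size justification, and the size of the error gives no ground for doubting the design.

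**What to change.** Keep 88 and correct the sentence in the Sample size calculation section, for example: *88 participants allow for about 6.8% dropout; at 10% dropout about 79 remain and power is slightly below 0.80 (about 0.79).* Beside it, state the test, the type of effect size, the number of measurements and the correlation entered in G-Power. The 0.79 comes from assumed settings, so the authors should confirm or replace it from their own G-Power run before printing it.

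The cost is one or two sentences and a slightly less favourable statement of power. No extra participants are needed, and the randomization list and envelopes stay as they are.

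If the authors prefer to keep the 10% allowance, the alternative is 46 per group (92 in total). That means 4 more participants, with the list and envelopes extended to 92 and the total changed in the Abstract. Given the small loss of power, correcting the sentence is enough.
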